#### Smoking outcomes

The primary outcome related to smoking will be 7-day point prevalence abstinence (i.e., no smoking at all in the past 7 days, not even a puff), which will first be assessed by self-report. If participants self-report ≥ 7-day abstinence, we will bio-verify their self-report. Saliva cotinine will be the primary bio-verification method (saliva cotinine of less than < 10 ng/ml will be considered abstinent) [61]. Saliva will be obtained from participants using the passive drool collection method and processed by Salimetrics using the salivary cotinine assay to determine the cotinine level present in the sample [62]. Participants will be instructed by research staff on how to prepare for and provide a sample of approximately 0.5 ml of passive drool. For those using nicotine replacement or noncombustible tobacco products, a carbon monoxide (CO) breath sample will be used to verify abstinence (CO < 6 ppm will indicate abstinence [61, 63]). Saliva samples and CO breath samples will be collected by mail if a face-to-face meeting is not possible. In person CO samples will be collected by research staff using the Covita Micro + Basic Smokerlyzer device [64] and remote CO samples will be collected using the Covita iCO Smokerlyzer [65], with telephone guidance provided by study staff. Secondary smoking outcomes will be 30-day point prevalence abstinence, continuous abstinence since discharge, and time from discharge to lapse (i.e., first puff) and relapse (i.e., smoking 7 consecutive days or in two consecutive 7-day periods). Participants who report using other combustible tobacco products will be considered smoking. Use of e-cigarettes and other non-combustible tobacco products (e.g., chewing tobacco) will be assessed at each timepoint and reported, but will not affect determination of abstinence.

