#### Retention and incentives for participation

Based on our pilot work and previous clinical trials in which we have obtained follow up completion rates of 85–90% (e.g., R01AT006948; K23HL107391; R44DA022167) [80, 81], we expect to complete follow-up assessments with at least 80–85% of participants. A comprehensive maintenance program similar to our previous studies will be used to ensure this level of retention.

Participants will receive $50 at each primary assessment completed [Baseline 1, Baseline 2, End-of-Treatment (12 weeks), and 6-, 9-, and 12-month follow-ups]. Transportation costs (taxi service, bus fare, mileage, and/or parking vouchers) to an in-person assessment will be paid for by the study. Participants will be paid $5 each for completion of counseling sessions 3, 4, 5, and 6 and a $20 bonus if that participant completes all four of these sessions. Remuneration for counseling sessions 3–6 was added (see Table 2) during the trial based on participant feedback that phone calls were using up limited cell phone minutes. For each brief phone assessment completed from 18 to 36 months post-discharge, participants will be compensated $10.

We will provide participants with study marketing materials (e.g., coffee mugs, water bottles, tote bags) that will include the study name, logo, phone number, and email. We will offer one item at Baseline 2 (1 week post-discharge) and one item at any follow-up assessment visit (12w, 6 m, 9 m, 12 m) attended in person. New Years and mid-Summer cards with the study logo will be sent to all study participants through the duration of their participation. Incentives and provision of marketing materials will be identical in each condition. We will send text, email, and/or mail reminders in advance of each assessment. We will obtain three “emergency contacts” (i.e., who will know how to reach the participant should their phone number be out of service) from each participant and these contacts will be updated as needed throughout the study.

Participants who do not have regular access to a phone or those who lose access to a phone during the first year of enrollment will be offered a study issued cellphone to complete study activities. Upon completion of the 12-month outcomes assessment, participants using study issued cellphones will be compensated $20 for returning the phone to study staff.

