##### Missing data

All analyses (other than the per protocol analyses detailed above) will be on the intent-to-treat sample (everyone randomized will be included in the final analysis) under various assumptions about the missing data mechanism. Sensitivity to these assumptions will be tested. Specifically, we will gather follow-up information and reasons for dropout regardless of protocol completion. We will compare the robustness of our findings using two statistical approaches for handling missing data. First, we will use inverse probability weighting with propensity scores. This is a two-step method: (1) using logistic regression, the probability of missingness is modeled as a function of baseline covariates and baseline values of the outcome and (2) the inverse of the propensity scores (predicted probabilities of dropout from the first step) serve as weights in our regression model of the outcomes. Provided the data is missing at random (MAR) or that the probability of missingness can be fully explained by observable data, this approach produces asymptotically unbiased estimates. To allow for the possibility that the MAR assumption may not hold, we will also use a second approach, pattern mixture models, in which the distribution of the outcome is assumed to follow a mixture of two distributions: one for those who complete follow up and another for those who do not.

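### Lost verification samples depend on the visit's self-reported abstinence, which neither planned missing-data approach uses, so an arm difference in sample return would bias the abstinence odds ratio undetected

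*Protocol article*

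**What the plan says.** Under Smoking outcomes, abstinence is taken first from self-report, and verification follows only for those who report it: "If participants self-report ≥ 7-day abstinence, we will bio-verify their self-report". Saliva cotinine is the main test, with breath carbon monoxide for users of nicotine replacement or non-combustible tobacco. Collection can be remote: "Saliva samples and CO breath samples will be collected by mail if a face-to-face meeting is not possible".

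Under Primary outcome analyses, verified abstinence at 12 weeks and 6, 9 and 12 months is modelled by GEE with a logit link, so the treatment effect is an odds ratio.

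Under Missing data, two approaches are named. In the weighting approach, "the probability of missingness is modeled as a function of baseline covariates and baseline values of the outcome", and the resulting scores are described as "predicted probabilities of dropout from the first step". The second approach, meant for the case where data are not missing at random, is a mixture of two distributions: "one for those who complete follow up and another for those who do not".

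Under Retention and incentives, the expectation is stated for assessments, not samples: "we expect to complete follow-up assessments with at least 80–85% of participants".

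**The concern.** A participant who reports smoking is classified once the interview is done. A participant who reports abstinence is not classified until a usable sample arrives. A mail kit that does not come back, too little saliva or a failed remote breath reading can therefore remove the outcome only from people who have just reported abstinence. Table 1 lists saliva and breath samples at every visit to 12 months without this condition, but that changes nothing, because a reported smoker is classified with or without a sample.

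This missingness is driven by something observed at the visit, the self-report, and the stated weighting model leaves it out. The section claims unbiased estimates only if data are missing at random or missingness is fully explained by observed data. A model restricted to baseline data does not meet that condition for lost samples.

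Sample loss is plausible here. Table 2 allows fully remote participation with mailed verification from September 2019, and records a continuing preference for remote visits when the blood measures were dropped in July 2021. At stake is the treatment effect on a co-primary outcome, and whether the planned sensitivity analyses would show a problem if there were one.

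**Working it through.** **Inputs.** From the Power section: 12-month abstinence of 29% (control) and 37% (BAT-CS), and a planned longitudinal odds ratio of 1.33. Sample return among abstainers is not given anywhere, so 80% to 90% is assumed.

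**The plan's own figure.** (0.37/0.63) / (0.29/0.71) = 0.5873/0.4085 = 1.438, which the article rounds to 1.4.

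**Formulas.** Let p be true abstinence and r the sample return among abstainers. In the base case every report of abstinence is true.
- Lost samples coded as smoking: observed rate = p·r.
- Lost samples set to missing: observed rate = p·r / (p·r + 1 − p). The odds are r·p/(1 − p), so the odds ratio equals the true one times r(BAT-CS)/r(control).

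**Equal return, 80% in both arms.**
- Set to missing: 0.232/0.942 = 24.6% versus 0.296/0.926 = 32.0%. The rates fall by 4.4 and 5.0 points; the odds ratio stays at 1.44.
- Coded as smoking: 23.2% versus 29.6%, odds ratio 1.39.
- If only 90% of reported abstainers would pass and return is unrelated to passing, set to missing gives 24.8% versus 32.3%, odds ratio again 1.44.

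**Unequal return, true odds ratio 1.44.**

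| Return, control / BAT-CS | Odds ratio, set to missing | Odds ratio, coded as smoking |
|---|---|---|
| 85% / 90% | 1.52 | 1.53 |
| 80% / 90% | 1.62 | 1.65 |
| 90% / 85% | 1.36 | 1.30 |
| 90% / 80% | 1.28 | 1.19 |

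For example, at 80%/90% set to missing, 1.438 × 0.9/0.8 = 1.62. With no true effect (29% in both arms) and 80%/90% return, the spurious odds ratio is 1.13 set to missing (0.9/0.8 = 1.125) and 1.17 coded as smoking.

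**Do the planned weights remove it?** A simulation of one million participants had one baseline covariate that predicted abstinence and dropout (about 15%). It weighted by the inverse probability of being observed, modelled on that covariate and arm. With dropout only, the weighted odds ratio was 1.44, as it should be. With sample loss added it was 1.44 at 80%/80%, 1.62 at 80%/90% and 1.29 at 90%/80%. The weights repair the dropout and leave the sample loss untouched.

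**Does the two-pattern mixture remove it?** If an interviewed participant without a sample counts as a completer, the model does not address that person. If they are grouped with the dropouts, two unlike groups are pooled. Take 85% assessment completion and 80%/90% return. In control, the no-sample group is 0.85 × 0.29 × 0.20 = 4.9% of participants, so 4.9/(15 + 4.9) = 25% of the pooled group has just reported abstinence. In BAT-CS it is 0.85 × 0.37 × 0.10 = 3.1%, or 3.1/(15 + 3.1) = 17%. The make-up of the pooled group differs by arm although dropout is identical, and one distribution for that group cannot show why.

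**The case against.** Four points on the other side deserve weight.

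*The plan may not be limited to dropout.* The first weighting step refers to missingness in general. The Outcome assessments section says that assessments to 12 months include biochemical verification, so a participant without a sample could count as not having completed follow-up. This stands as a reading, and a reader should not infer that the plan ignores lost samples outright. It does not rescue the methods: baseline predictors still omit the self-report, and the pooled pattern still mixes unlike groups. A wide enough arm-specific range for that pattern might happen to cover the truth, but it would not identify sample loss as the cause.

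*Abstinence need not be biased downward.* A reader might infer that it must be. People who report falsely have a reason not to return a kit. With 29% truly abstinent and 0.29/0.9 = 32.2% reporting it, if only the false reporters (3.2%) fail to return, setting losses to missing gives 0.29/(1 − 0.032) = 30.0%, which is too high. Coding them as smoking gives exactly 29%.

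*Return may well be equal.* Assessors are blinded, sessions are matched on length, timing and medium, incentives are identical, and staff guide the remote breath test by telephone. The documents contain no evidence of an arm difference. This stands; the unequal-return figures are scenarios.

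*The coding rule may be in the full protocol or the SAP.* This also stands: its absence from a journal article is not a finding. But neither coding as smoking nor setting to missing removes the bias from unequal return.

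**Conclusion.** The point holds as a mismatch between two things that the article does state: a verification rule that makes sample loss depend on the visit's self-report, and two missing-data approaches that do not use it. If return differs by 10 points between arms, an odds ratio of 1.44 would appear as about 1.2 to 1.3 or about 1.6 to 1.65, depending on direction and coding; a 5-point difference gives about 1.30 to 1.36 or 1.52 to 1.53. Against a planned longitudinal odds ratio of 1.33, shifts of this size matter. If return is equal and losses are set to missing, the odds ratio is essentially unchanged, and only the rates and the risk difference are likely to shrink.

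These figures rest on assumed return rates and on return being unrelated to whether the sample would pass. The article supports neither a claim that the effect is biased nor a claim about direction. It supports the claim that such a bias would be neither corrected nor revealed by the two approaches as described.

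**What to change.** In the Missing data section, separate two kinds of missing abstinence outcome: no interview, and abstinence reported without a usable sample. Keep the stated methods for the first.

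For the second, add a sensitivity analysis conditioned on the visit's self-report. This can be multiple imputation of pass or fail, or weights estimated among self-reported abstainers, using arm, visit, collection mode, nicotine-product use and verified status at other visits. Imputation alone is not enough: in the scenario where only false reporters withhold samples, every returned sample passes, and imputation would give 32.2% against a true 29%. So also vary the pass probability of unreturned samples from 0 (coded as smoking) to 1, separately by arm. Coding all of them as smoking in both arms does not bound the arm difference, as the spurious 1.17 under no effect shows. Report sample return among self-reported abstainers by arm.

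The cost is plan wording and modest programming. The self-report is already collected at every visit; collection mode would come from study records. The downside is an untestable assumption about unreturned samples and a possibly wide range. At 80%/90% return, with all reports true, the extreme corners are (0.333/0.667)/(0.29/0.71) = 1.22 and (0.37/0.63)/(0.232/0.768) = 1.94, around a true 1.44. That width shows how much the conclusion depends on the lost samples.

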## Discussion

Approximately 400,000 ACS patients who smoke are discharged from the hospital annually in the US [1–3]. Thus, even modest improvements in the rate of smoking cessation post-ACS could save thousands of lives [87]. Moreover, results of this study may also provide insight into the role of smoking in the relationship between depression and cardiac morbidity and mortality in ACS patients and provide a model for how to investigate the role of other health behaviors in this relationship (e.g., diet, physical activity, medication adherence). The work of integrating treatments that can address both psychological distress and health behavior changes into existing medical systems and discovering sustainable models is crucial to long-term intervention impact. If this study shows BAT-CS to be efficacious for smoking, we plan to propose a multi-site effectiveness study focused on integration into ongoing hospital systems, cost-effectiveness, and long-term sustainability.

## Data Availability

The deidentified dataset will be made available 18 months after study closure to interested investigators who submit a written request. We will publish the results in academic journals and results will be posted on clinicaltrials.gov.

## Abbreviations

ACS: Acute coronary syndrome
BA: Behavioral activation
BADS: Behavioral activation for depression scale
BAT-CS: Behavioral activation for cardiac smokers
CO: Carbon monoxide
CSQ-8: Client satisfaction questionnaire
DASI: Duke Activity Status Index
FTND: Fagerström test for nicotine dependence
GEE: Generalized estimating equations
GRACE: Global registry of acute coronary events
MACE: Major adverse cardiac events
MAR: Missing at random
MMSE: Mini-mental state exam
PANAS: Positive affect negative affect scales
PES: Pleasant events schedule
PHQ-9: Patient health questionnaire
PSS-4: Perceived stress scale
RCT: Randomized control trial
SCAD: Spontaneous coronary artery dissection
SF-12: Short form health survey
SHAPS: Snaith hamilton pleasure scale
